## METHODS AND STUDY DESIGN

A randomized trial (RCT) is at the core of Grand Challenge 2, involving **48 infants** with CP between 6 and 18 months. Inclusion criteria will include: being diagnosed or considered at high risk of unilateral (RCT1) cerebral palsy, 6 to 18 months inclusive and ability to complete testing according to the age. Exclusion criteria will include epilepsy, botulinum toxin injections or orthopedic surgery within the past six months or during the study period, as well as severe visual and cognitive impairments preventing the child from being interested in simple games.

A pair-matched randomization will be used. Group allocation to either HABIT-ILE or a control condition will be randomly determined within each pair. As depicted in Figure 3, the HABIT-ILE group (n=24) will receive 50 hours of treatment over 2 weeks (5 h/day, 5 days/week) whereas the control group (unilateral n=24) will follow their usual activities for 2 weeks (nursery, ongoing therapy, generally a few hours of neurodevelopmental therapy per week, etc.). Usual activities have been chosen as control intervention since spontaneous activity of infants is oriented towards the discovery of their environment with motor activities in a nursery reaching around 5 hours per day. The between-group comparisons will be carried out between T0 and T+15 and between T0 and T+90. Participants in the control group will be offered HABIT-ILE training after assessment period 3. A supplementary assessment of this group at T0+180d will allow us to investigate the influence of the onset of therapy time and persistence of the therapeutic effects on the long term.

Each assessment will comprise clinical outcomes, biomechanical assessment, and neuroimaging outcomes (traditional and multi-shell HARDI DW-MRI).

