## STATISTICAL ANALYSIS

No DTI pre-post intervention analyses in infants have been published so far. However, since CST integrity measured with DTI is highly correlated with manual ability (Bleyenheuft et al., 2007), we performed a sample size calculation based on the AHA score of the pilot study performed in 10 infants with unilateral CP (see “pilot data”). A mean improvement of 8,2 AHA units (standard deviation=5.9 AHA units) after the intensive therapy was reported. Thus, our hypothesis is an incremental improvement of 1 SD between the HABIT-ILE group and the control group (between group difference =7,2, SD=5,9). With  $\alpha=0.05$  and a  $1-\beta=0.9$ , a sample size of **15 participants per group is required**. Considering potential drop-outs and data loss in MRI, **24 participants will be included in each group**. Neuroplastic changes and secondary outcomes will be compared between groups using analysis of variance (ANOVA). Non-parametric methods will be performed whenever ANOVA assumptions are not met. Time-onset influence will be tested at the 4th assessment using an ANOVA.

Separate generalized linear models (GLM) will be estimated for the CST and whole-brain WM (ICTEAM models) to infer the correlations between  $\mu S$  integrity at baseline/after intervention and the MskL outcomes (bimanual SAT). Finally, an overall GLM will be estimated to combine CST and whole-brain  $\mu S$  integrity. The *R* software will also be used for bimanual MskL curves modelling.

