## METHODS AND STUDY DESIGN

In order to compare HABIT-ILE with the recovery of motor control during a time equivalent control period involving standard activity and conventional rehabilitation, we will run a single-blind randomized clinical trial (RCT) similar to Grand Challenge 2 with a parallel, cross-over group design (see Figure 5). The stroke patients will be randomly assigned either to a HABIT-ILE therapy for 10 days (5 days a week, 5 hours per day during 2 weeks; total = 50 hours) or to the time-equivalent control period with a minimization software to stratify patients for plegia/paresis/no motor deficit, gender, age, stroke in the (non-)dominant hemisphere, etc. The control group will follow its usual rehabilitation care and document all activities and therapeutic interventions during the initial 2-week period. A complete assessment will be performed for both groups before (T0) and after (T0+15d) the intervention/control period as well as 3 months post-intervention (T0+90d). An additional assessment will be added for the control group at the end of their delayed HABIT-ILE intervention, allowing us to collect data reflective of the effect of HABIT-ILE from a larger group. Each assessment will comprise clinical assessments, robotic measurements and neuroimaging data including multi-shell HARDI DW-MRI to be analyzed using ICTEAM frameworks for the extraction of WM  $\mu$ S indices.

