## STATISTICAL ANALYSIS

Since HABIT-ILE has never been applied in adult stroke patients, we based our sample size on motor changes observed previously in in school-aged children with brain lesions. We performed a sample size calculation based on the UL changes observed in the assisting hand assessment (AHA) [ref Bleyenheuft et al, 2015]; we expect a similar effect size here. Thus, our hypothesis is an incremental improvement of 1 SD between the HABIT-ILE group and the control group (between group difference=6, SD=5). With  $\alpha=0.05$  and a  $1-\beta=0.9$ , a sample size of 16 participants per group is required. Considering potential drop-outs and data loss in MRI, **24 participants will be included in each group**. Neuroplastic changes and secondary outcomes will be compared

759 between groups using analysis of covariance (ANCOVA) to adjust for baseline measurement. Non-parametric  
760 methods will be performed whenever ANCOVA assumptions are not met.

761 The *R* software will be used under the supervision of statisticians for pre-specified stat. analyses as we did  
762 before [46,47, 57]. Separated generalized linear models (GLM) will be estimated for the CST and whole-brain  
763 WM (ICTEAM models) to infer the correlations between  $\mu$ S integrity at baseline/after intervention and the  
764 MSkL outcomes (bimanual SAT). Finally, an overall GLM will be estimated to combine CST and whole-brain  $\mu$ S  
765 integrity. The *R* software will also be used for bimanual MskL curves modelling.

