- 2) The so-called resolution limit for axon diameters is a fundamental limitation of present-day DW-MRI technology, irrespective of the mathematical model used. However, the new GE scanner installed at Saint-Luc will deliver gradients up to 80 mT/m, the highest for any clinical system and a major improvement from the previous generation of MRI scanners, typically limited to 40-60 MT/m. Studies of sensitivity to microstructural features based on hardware constraints have been performed before and will be repeated during the preparation of DW-MRI sequences for this study, in collaboration with [name] and the MRI physicist appointed by the MRI manufacturer [SPIE16]. Those studies will clearly delineate the uncertainty on our estimates of axon diameters. Of note is that our Microstructure Fingerprinting approach was based on the most accurate modeling approach available and was specifically designed to enhance sensitivity to axon diameter. Other microstructural features of importance such as axonal orientation and axonal density, expected to play a crucial role in the reorganization of the CST during neurorehabilitation, are much less affected by gradient strength and do not suffer from the transition to clinical settings. Finally, predictive biomarkers of motor recovery

can be found even if a bias persists between the biological groundtruth and the DW-MRI –based  $\mu S$  estimates.

3) We will perform night MRIs with less noisy machines, shorter scanning sequences (possible thanks to a new equipment in our University Hospital Saint-Luc, Woluwe), very careful routines for gradual adaptation, specific installation and material for the infants. Repetitive MRIs under such conditions are successful in at least 70% of the infants[109].

4) We will provide time for participant before training to meet the team and discover the environment. Special attention will be paid in adults to the accessibility of the treatment room and the moment of the year the training will be performed (avoiding risks of contamination between fragile patients). Special attention will be paid for infants to the bonding with one therapist and providing routines during the day. Highly stimulating toys presented at the limit of reaching in the direction of movement expected and positive reinforcement will be used. These ingredients were successful in our pilot study including 4 children aged 12 to 18 months.

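### The ANOVA and ANCOVA stated for imaging and secondary outcomes leave out the infant pairs and the adult minimisation factors, which wastes precision if those factors predict outcome

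*Protocol*

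**What the plan says.** **Infants (Grand Challenge 2).** Methods and Study Design: "A pair-matched randomization will be used. Group allocation to either HABIT-ILE or a control condition will be randomly determined within each pair". The matching variables are not named. Statistical Analysis: "Neuroplastic changes and secondary outcomes will be compared between groups using analysis of variance (ANOVA". No pair effect is mentioned, and the sample size is for two groups with no allowance for pairing.

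**Adults (Grand Challenge 3).** Methods and Study Design allocates patients "with a minimization software to stratify patients for plegia/paresis/no motor deficit, gender, age, stroke in the (non-)dominant hemisphere, etc". Statistical Analysis compares arms "between groups using analysis of covariance (ANCOVA) to adjust for baseline measurement". No other covariate is named.

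Both analysis sentences refer to imaging (neuroplasticity) outcomes and secondary outcomes. Neither section names a between-group test for the primary clinical outcomes, the mini-AHA and the ad-AHA.

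**The concern.** Matching and minimisation force the arms to be alike on chosen characteristics. Where those characteristics predict the outcome, the difference between arms varies less from one randomisation to the next than it would under simple randomisation. An analysis that omits the pairs or factors still counts that variation as error. The standard error is then larger than the true one, confidence intervals are too wide, and the test rejects less often than its nominal level.

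At stake is the precision that the allocation was meant to buy. It matters most for the imaging outcomes: the protocol says no pre-post DTI analyses in infants have been published, so their effect size is unknown, and some scans are expected to fail.

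**Working it through.** **1. The plan's own figures.** Inputs for infants, from Grand Challenge 2, Statistical Analysis: "between group difference =7,2, SD=5,9", alpha 0.05 (taken as two-sided), power 0.90.

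n per group = 2 × (1.960 + 1.282)² × (5.9/7.2)² = 14.1, rounded up to 15. This matches "a sample size of 15 participants per group is required". A t-based calculation gives 15.1. For adults (difference 6, SD 5) the t-based calculation gives 15.6, rounded up to the stated 16. Both figures follow from an independent-groups formula.

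**2. Infants: formula.** Let rho be the within-pair correlation of the analysed quantity. With 24 pairs and SD 5.9:

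- SE assumed by the unpaired ANOVA = 5.9 × sqrt(2/24) = 1.70
- true SE = 5.9 × sqrt(2 × (1 − rho)/24)
- ratio = 1/sqrt(1 − rho)

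The documents give no rho, so a range is assumed. Type I error and power come from 100,000 simulated trials per value. The smaller effect of 4 units (4/5.9 = 0.68 SD) is also an assumption.

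| rho (assumed) | True SE | SE overstated by | Actual level of unpaired 0.05 test | Power for 4 units, unpaired / paired |
|---|---|---|---|---|
| 0 | 1.70 | 0% | 0.050 | 0.63 / 0.61 |
| 0.1 | 1.62 | 5% | 0.039 | 0.64 / 0.66 |
| 0.2 | 1.52 | 12% | 0.029 | 0.65 / 0.71 |
| 0.3 | 1.42 | 20% | 0.020 | 0.66 / 0.77 |
| 0.5 | 1.20 | 41% | 0.007 | 0.68 / 0.89 |

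The paired analysis holds about 0.05 throughout. As a check, the normal approximation 2 × (1 − Phi(1.96/sqrt(1 − rho))) gives 0.019 at 0.3 and 0.006 at 0.5.

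**3. Adults.** The pair formula does not apply to a baseline-adjusted ANCOVA after minimisation, so this was simulated: 48 patients, one three-level and three two-level factors, and allocation to the better-balancing arm with probability 1 or 0.8 (3,000 trials per setting). The share of variance that the factors explain after baseline is assumed.

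| Share explained after baseline | Actual level, baseline only | Actual level, factors added |
|---|---|---|
| 0% | 0.049 | 0.048–0.049 |
| 10% | 0.036–0.045 | 0.045–0.052 |
| 30% | 0.022–0.023 | 0.051–0.054 |
| 50% | 0.009–0.015 | 0.049–0.050 |

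**4. The planned clinical difference.** The protocol states "24 participants will be included in each group". With 24 per group an unpaired t-test has power 0.985 for 7.2 units (infants) and 0.983 for 6 units (adults). Positive rho raises the infant figure.

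**The case against.** **The protocol does not exclude these terms.** An ANOVA with pair as a block is still an ANOVA, and an analysis plan that is not shown may list more covariates. This stands in part: a reader might infer that the protocol expressly treats the 48 infants as independent, and it never says so. But it does name the test and, for adults, the one adjusting covariate. Anyone following that wording would leave the design out.

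**The excess may be small or nil.** This stands. No correlation is given, the matching variables are unnamed, and comparisons from T0 to later visits suggest change scores. Matching on baseline traits need not make two infants' changes correlate. A reader might infer that the standard errors are certainly too wide; the documents support only the conditional statement, so the table starts at rho = 0.

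**The infant percentages do not carry over to adults.** This also stands. Baseline adjustment already absorbs part of what the minimisation factors explain.

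**The harm is modest.** Agreed. Omitting these terms makes the tests conservative and does not produce excess false positives.

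**Conclusion.** The point holds in conditional form. For imaging and secondary outcomes, the stated ANOVA and baseline-only ANCOVA do not reflect how participants are allocated. If the matching or minimisation factors predict the outcome, precision is lost. In infants the standard error is overstated by 5% to 41% for assumed within-pair correlations of 0.1 to 0.5, and by nothing at 0. In adults the nominal 0.05 test runs at about 0.036 to 0.045 if the factors explain 10% of the variance left after baseline, and about 0.022 if 30%. All these inputs are assumptions.

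Two stronger readings should be resisted. The primary clinical comparison is not shown to be affected, since no test is named for it and power at the planned difference is at least 0.98 with 24 per group. Nor does the protocol plan a complete-pair test, so the loss of pairs through failed scans is no fault of the stated analysis; it bears only on the choice of remedy.

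**What to change.** **Infants.** Name the matching variables. Analyse with a linear mixed model containing arm, baseline and a random effect for matched pair. A plain paired test is the poorer remedy because it drops an infant whose partner's data are missing. The protocol's risk section expects: "Repetitive MRIs under such conditions are successful in at least 70% of the infants". At exactly 70%, with independent failures, 24 × 0.7² = 11.8 complete pairs would remain, against 24 × 0.7 = 16.8 infants per arm. As 70% is a lower bound, the loss could be smaller. The mixed model keeps the unpartnered infants.

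**Adults.** Replace the open-ended list with the minimisation factors actually used, and add them to the ANCOVA alongside baseline.

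**Cost.** A wording change, a few degrees of freedom, and a slight loss of power if the factors predict nothing (0.63 to 0.61 for the assumed 4-unit effect, with a paired test as the comparator).

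**Separately.** The adult minimisation list includes a level for patients without a motor deficit, while the inclusion criteria require hemiparesis. The two passages should be reconciled. This has no bearing on the standard errors.

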## PROCEDURES/METHODOLOGIES

The intensive motor skill training consists of an adaptation of HABIT-ILE. This intervention, which we developed initially for children with CP over 6 years old, is carried out in a camp setting, with structured tasks of increasing motor difficulty and functional activities that require the use of both hands whilst sustaining postural activity or activities of the lower extremities. The therapy, using games and functional activities, is delivered in a child-

friendly environment. The tasks are chosen according to individualized functional goals previously defined by the parents (e.g. drinking or sitting autonomously, playing without help, etc.).

Although the basic principles of HABIT-ILE will be followed (Bleyenheuft & Gordon, 2014), the toys, tasks and activities will be adapted to induce spontaneously bimanual use. The duration of activities as well as lower extremities/postural associations will also be adapted to each infant depending on his/her functional objectives and personal characteristics (motor and attentional level, for instance). Eight to ten infants will undergo rehabilitation during one intensive session of 2 weeks; each infant will have a full-time therapist dedicated to his/her treatment. The follow-up of the guidelines and the fidelity to the treatment principles will be ensured through the supervision of all interventions by the post-doctoral coordinator dedicated to the project. As 50 to 60 hours of intensive therapy are needed to induce long-term motor changes (Brandão et al., 2018; Sakzewski et al., 2015), this project, in agreement with the usual motor activity time (Van Cauwenberghe et al., 2011) and the need for infants to rest, includes 5 hours per day of therapy with the same therapist for a total of 50 hours. HABIT-ILE for infants has been tested in a pilot study (illustrations in section “pilot results”) which has confirmed previous evidence that this therapy intensity is both practically feasible and efficient for children that age (Taub et al., 2004).

The time-equivalent control period consists of the child’s usual activity, including nursery, usual rehabilitation, etc. Both the content of this activity (notebook) and the time of activity (wearable sensors used in both groups to monitor the amount of movements) will be documented. This approach enables the comparison of the structured aspect of motor activities in therapy compared and “spontaneous activities” to be carried out.

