## GRAND CHALLENGE 4: EXPLORING MECHANISMS OF TRAINING-INDUCED FUNCTIONAL RECOVERY THROUGH WM MICROSTRUCTURE IN VERY EARLY LESIONS VS ADULT ACQUIRED LESIONS

The identical experimental settings of WP 2 and 3 make it possible to directly compare WM baseline damage and training-induced changes between hemiplegic CP infants and adult stroke patients, both at the macroscopic level using whole-brain tractography and at the microscopic level using voxel-wise, model-based microstructural features. The deep underpinning of the differential repair mechanisms based on the initial conditions and age of the patients is likely to bring neurophysiological responses to the conditions allowing WM repair or training-induced changes. Investigating the best responders depending on initial conditions should help to better tailor treatment to each patient.

### RESEARCH HYPOTHESES OF GRAND CHALLENGE 4

Grand Challenge 4 will test the following hypotheses:

1. Experience-induced remodeling of the damaged CST occurs both in CP infants and adult stroke patients undergoing HABIT-ILE, but is stronger in developing CP infants **(HP4.1)**;
2. Neuroinflammation quantified by DW-MRI biomarkers is more predominant in developing CP infants compared to chronic adult stroke patients **(HP4.2)**.  
In both adult stroke patients and CP infants,
3. response to HABIT-ILE correlates *positively* with baseline DW-MRI markers quantifying the residual integrity of the damaged CST **(HP4.3)**;
4. response to HABIT-ILE correlates *negatively* with baseline DW-MRI markers quantifying a baseline enhancement of the ipsilateral, uncrossed CST **(HP4.4)**;
5. Combining DW-MRI  $\mu S$  markers of the CST with a whole-brain index of WM  $\mu S$  integrity correlates more closely with clinical response to HABIT-ILE than using exclusively the DW-MRI markers of the CST **(HP4.5)**.

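### The T0+180d visit in delayed-treatment infants cannot show long-term persistence, the protocol disagrees on who attends it, and the delayed phase is not identical in the two trials

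*Protocol*

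**What the plan says.** **Infant trial (Grand Challenge 2, Methods and study design).** The immediate arm receives "50 hours of treatment over 2 weeks". For the other arm, "Participants in the control group will be offered HABIT-ILE training after assessment period 3", that is, after T0+90d. No start date or window is given. Then: "A supplementary assessment of this group at T0+180d will allow us to investigate the influence of the onset of therapy time", and also the "persistence of the therapeutic effects on the long term". The randomised comparisons run from T0 to T0+15d and from T0 to T0+90d.

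**Infant trial, elsewhere.** The Statistical analysis section tests the influence of therapy onset with an ANOVA at the fourth assessment, which serves HP2.4. Under Operating costs (Part 2), the MRI count gives four assessments to each of 48 children. It gives three to each of 48 adults, plus 24 for adult controls.

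**Adult trial (Grand Challenge 3, Methods and study design).** "An additional assessment will be added for the control group at the end of their delayed HABIT-ILE intervention". The stated aim is to gather HABIT-ILE effect data from more patients, not to study persistence. Procedures/Methodologies calls this visit the final one.

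**Cross-population comparison.** Grand Challenge 4 opens with: "The identical experimental settings of WP 2 and 3 make it possible to directly compare WM baseline damage and training-induced changes". Item 4 of the list of grand challenges, and the hypotheses section of Grand Challenge 3, also describe the settings or core design as identical. The adult methods section says only that the trial is similar.

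**The concern.** Three things are at stake.

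- **Persistence.** The visit is dated from T0, while the delayed infants' training is dated only as some time after T0+90d. The time since training at T0+180d is therefore short, variable and not fixed by the protocol. With no measurement at the end of that training, nothing separates what was gained from what was kept.
- **Onset (HP2.4).** Which infants are compared at the fourth assessment depends on which section is followed. If only controls attend, the ANOVA has no concurrent early-onset group. If both arms attend, the groups differ in time since training as well as in onset.
- **Infant-adult comparison.** The one extra visit in the delayed phase sits at a different time after training in each trial. Delayed-arm data used across populations on the strength of the word *identical* could turn a difference in lag into an apparent difference in plasticity.

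**Working it through.** **1. Visit count, reproducing the budget.** Inputs are from Operating costs.

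- Infants 48 × 4 = 192; adults 48 × 3 = 144; adult controls 24.
- 192 + 144 + 24 = 360, and 360 × EUR 181.5 = EUR 65,340, as budgeted. The 358 in the same sentence is not the sum of its own terms.
- If only control infants had the fourth visit: 24 × 3 + 24 × 4 = 168 infant visits, and 168 + 144 + 24 = 336 overall.

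The budget therefore assumes a fourth visit for all 48 infants, while the design text gives it to the control group. Four visits per child leave no room for an end-of-training visit in the delayed arm. Three plus one per adult control leave no room for a visit after the end-of-training one.

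**2. Time since training.** Training is taken as 15 days, following the T0 to T0+15d convention. Taking 14 days adds one day to each interval below that is counted from the end of training. Let w be the days between T0+90d and the start of the delayed camp.

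- Immediate arm at T0+90d: 90 − 15 = 75 days.
- Immediate arm at T0+180d, if it attends: 180 − 15 = 165 days.
- Delayed arm at T0+180d: 180 − (90 + w + 15) = 75 − w days.

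| w (days) | Delayed infants: days since training at T0+180d |
|---|---|
| 0 | 75 |
| 14 | 61 |
| 28 | 47 |
| 42 | 33 |
| 75 | 0 |

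The values of w are illustrative, since the protocol gives no start window. Some wait is plausible because training is given in camps: "Eight to ten infants will undergo rehabilitation during one intensive session of 2 weeks". The 24 controls fill 24/10 = 2.4 to 24/8 = 3 sessions' worth of places.

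**3. What T0+90d to T0+180d can show in the delayed arm.** T0+90d is before training and T0+180d is 75 − w days after it, with nothing in between. The change is training gain, minus any later loss, plus 90 days of development. The net change can be estimated; its parts cannot.

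**4. The onset ANOVA if both arms attend.** Time since training is 165 days against 75 − w, a difference of 90 + w days. At a fixed time since T0, later onset necessarily means less time since training, so the two cannot be separated at this visit.

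**5. The two trials side by side.**

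| Visit | Infants | Adults |
|---|---|---|
| T0, T0+15d, T0+90d | yes | yes |
| Extra visit, delayed arm | T0+180d, 75 − w days after training | end of delayed training, about 0 days |

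**The case against.** The strongest reply is that the budget and the fourth-assessment ANOVA both point to a T0+180d visit in both arms. The immediate arm would then be seen about 165 days after training with T0+15d as its reference, which does bear on longer-term persistence. This stands. It would be wrong to infer that the infant trial as a whole cannot address persistence. What remains is that there would be no untreated comparator by then, and that the design text attaches the claim to the control group.

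Second, the first purpose given for the visit is the onset question. Dating it from T0 keeps time since T0, and hence development, comparable between arms. Moving it to a fixed interval after delayed training would equalise lag but let time since T0 vary with camp date. This stands too: the T0 anchor is a defensible trade-off, not an error.

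Third, the delayed arm does have a pre-training value at T0+90d, so a net gain at T0+180d is interpretable as such. Agreed.

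Fourth, a reader might infer that Grand Challenge 4 fails, or that up to 24 of 48 participants per trial will enter it at unmatched lags. The protocol does not support this. Nowhere does it say that delayed-arm data enter the infant-adult comparison. The wish for a larger group is stated for the adult trial only, and the three shared visits suffice for baseline damage and training-induced change. The adult extra visit is not claimed to show persistence either.

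Finally, Figures 3 and 5 are not available in the text reviewed and might show timing. The budget count argues against further visits.

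**Conclusion.** The point holds in a limited form.

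- The delayed infants cannot support a long-term persistence claim. Their last visit is at most about 75 days after training, no later than the immediate arm already reaches at T0+90d, and no end-of-training value exists.
- The design text, the analysis section and the budget disagree on who attends at T0+180d (336 or 360 assessments overall). If both arms attend, the onset ANOVA carries a difference in time since training of at least about 90 days.
- *Identical* is untrue for the delayed phase (about 0 days in adults, at most about 75 in infants) but true for the schedule of T0, T0+15d and T0+90d.

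The randomised comparisons and the sample size are unaffected. The figures assume 15 days of training and a delayed camp starting no earlier than T0+90d. How far the lag falls below 75 days depends on a start window that the protocol does not state.

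**What to change.** 1. Reconcile the infant design text, the fourth-assessment analysis and the budget on who has the T0+180d visit, and correct 358 to 360 or to whatever total follows.
2. Take persistence only from the immediate arm: T0+15d to T0+90d, described as about 75 days after training, and T0+180d if that arm attends, described as about 165 days after training and without an untreated comparator. Remove the long-term persistence claim from the delayed arm, and describe its T0+90d to T0+180d change as a net gain.
3. Record the end date of delayed training for each control infant and report time since training alongside the onset ANOVA, stating that onset and lag are tied at that visit.
4. In Grand Challenge 4, restrict infant-adult response comparisons to T0, T0+15d and T0+90d, or use delayed-arm data only at matched lags. Limit the word *identical* to the shared visits wherever it is used.

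Keep the T0+180d visit anchored to T0.

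The cost is rewording and one recorded date per control infant. Whether the visit count changes depends on how item 1 is settled; the existing budget already covers a fourth visit for all 48 infants. The price is a narrower persistence claim and possibly fewer delayed-arm records in cross-population analyses.
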